### Participant Recruitment

Participants are recruited in schools, school holiday programs, music schools, and sports clubs via personal communication, newspapers, and email distribution lists of the Karlsruhe Institute of Technology. Power analyses for analysis of covariance with 2 groups and 4 covariates using G*Power [52] yields a total of 52 families with approximately N=156 participants (assuming 3 family members), to find a small-to-medium effect (α=.05, 1-β=.80, Cohen *f*=0.25). In order to increase power and to compensate for potential dropouts, we aim for a total of 60 families per trial. Please see Figure 3 for the planned participant flow for SF and SF2.0.

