### Data Analysis

First, the baseline characteristics of the study population are summarized within each cluster randomized group on individual and family levels for all measures to control for group differences. Then, all primary outcome data will be screened for normal distribution by using the Shapiro-Wilk test. Data will be checked for outliers. To further analyze changes in health behavior, mixed-model analysis of covariance with time (T_0_ and T_1_ for device-based physical activity; T_0_, T_1_, and T_2_ for self-reported physical activity and healthy eating) as within-subjects and group (intervention group vs control group) as between-subjects factor will be conducted, with covariates being family health climate, self-efficacy, and intrinsic motivation (Behavioral Regulation in Exercise Questionnaire and Regulation of Eating Behavior Scale) as well as intention in SF2.0. Results of the Mauchly test will be checked for homoscedasticity of data and results will be corrected accordingly (ε>0.75 Huynh-Feldt, ε<0.75 Greenhouse-Geisser). Furthermore, homogeneity of the error variances will be checked, as assessed by Levene test. If this test does not reveal significance, a Box-Cox transformation will be applied to the data. Moreover, Tukey-corrected posthoc tests will be considered for detailed interpretation of results. Main effects will only be considered if the interaction is found to be significant. All analyses will be conducted using SPSS 26 statistical software (IBM Corp).

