## Discussion

### Overview

The aim of the SF project is the development, implementation, evaluation, and refinement of an mHealth intervention to increase physical activity and healthy eating at individual and family level. Extending the previous research, the behavior of children *and* parents is targeted in order to induce individual behavior changes that are anchored in daily family life. Moreover, several behavior change techniques were included, which contribute to the fulfillment of the basic psychological needs according to the self-determination theory [46,47]. We examined whether (1) mHealth interventions (SF, SF2.0) elicit meaningful increases in physical activity levels and healthy eating in children as well as adults as compared to controls (no mHealth intervention), (2) changes are maintained after the intervention period, and (3) intervention effects can be strengthened by the addition of app-based features and JITAIs (SF2.0).

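### The interpretation rule is the wrong way round: it turns to main effects when the group-by-time interaction is significant, where neither main effect estimates the treatment effect

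*Protocol article*

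**What the plan says.** All statements are in the protocol article.

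- **Model (Data Analysis).** A mixed-model analysis of covariance has time "as within-subjects and group (intervention group vs control group) as between-subjects factor will be conducted". The occasions are "T_0_ and T_1_ for device-based physical activity" and "T_0_, T_1_, and T_2_ for self-reported physical activity and healthy eating".
- **Follow-up (Data Analysis).** "Tukey-corrected posthoc tests will be considered for detailed interpretation of results". The comparisons are not named.
- **Interpretation rule (Data Analysis).** The next sentence reads: "Main effects will only be considered if the interaction is found to be significant". Time and group are the only factors, so the interaction meant is group by time.
- **Questions (Discussion, Overview).** The first is whether the apps "elicit meaningful increases in physical activity levels and healthy eating in children as well as adults as compared to controls". The second, listed separately, is whether "changes are maintained after the intervention period".

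The section does not say that the interaction is the test of the intervention effect.

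**The concern.** The usual rule runs in the opposite direction. If group by time is significant, the group difference is not the same at every occasion, so one reads the differences at each occasion (the simple effects) and not the averages over occasions (the main effects). The article turns to the averages in exactly that situation.

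Two things are at stake:

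- **Size of the effect.** If the rule is followed literally, a trial that has found an effect goes on to look at quantities that understate it. The shrinkage also depends on how long the effect lasts. The article expects larger effect sizes in SF2.0 than in SF. If group main effects fed that comparison for self-reported outcomes, differences in size and in persistence would be confused.
- **Separation of the two questions.** With three occasions, a single interaction test covers both the effect at T1 and its persistence at T2. A significant result does not say which question has been answered.

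**Working it through.** The article attaches no figure to this rule, so there is none to reproduce. Its sample-size calculation does not bear on the point.

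**Inputs**
- From Data Analysis: two groups; two occasions for accelerometer outcomes; three for self-reported activity and healthy eating.
- From the design: T0 precedes the intervention, so under randomisation the expected group difference at T0 is δ0 = 0.
- Illustrative effect: δ1 = 0.50 SD at T1. This is the standardised difference matching the Cohen f of 0.25 in Participant Recruitment (for two equal groups d = 2f = 2 × 0.25 = 0.50).
- Assumed, because the article gives no figure: the effect at T2 is either gone (δ2 = 0) or fully kept (δ2 = 0.50).

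**Step 1. Group main effect = mean of the group differences over occasions**

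| Model | Calculation | Group main effect | Share of the T1 effect |
|---|---|---|---|
| T0, T1 | (0 + 0.50)/2 | 0.25 SD | 50% |
| T0, T1, T2, effect gone at T2 | (0 + 0.50 + 0)/3 | 0.17 SD | 33% |
| T0, T1, T2, effect kept at T2 | (0 + 0.50 + 0.50)/3 | 0.33 SD | 67% |

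**Step 2. Time main effect = change averaged over the two arms**

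For T0 to T1, with a change of 0.50 SD in the intervention arm and 0 in the control arm: (0.50 + 0)/2 = 0.25 SD. This is not a comparison with control.

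**Step 3. Does a significant interaction repair these values?**

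A simulation of 4000 runs per scenario assumed 64 people per arm, within-person correlation 0.5, no covariates and no family clustering. Among runs with a significant interaction, the mean group main effect was 0.244 SD (two occasions), 0.167 SD (three, gone at T2) and 0.336 SD (three, kept). Selecting on the interaction leaves the dilution in place. In those same runs the group main effect was itself significant in only 37%, 21% and 64%.

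**Step 4. What the interaction tests**

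- *Two occasions.* It has 1 df and tests δ1 − δ0 = 0, which is the between-group contrast of T1-T0 change. In the simulation its p-value equalled that of the change contrast to rounding error (largest difference about 1e-15), and both were significant in 80% of runs.
- *Three occasions.* It has 2 df and tests δ0 = δ1 = δ2. With a difference of 0.50 SD at T2 only, it was significant in 84% of runs, against 5% for the T1-T0 contrast. A significant interaction therefore does not by itself answer the first research question.

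**The case against.** **The rule may be loose wording for simple effects.** That is possible, and the repair would then be very small. But nothing in the article says so, and as written it directs the analyst to main effects.

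**The rule does not make main effects the efficacy test.** This stands in part. By making main effects conditional, it uses the interaction as the gate, which is the right place to look for the intervention effect. When the interaction is not significant, it also stops a change common to both arms from being read as efficacy. A reader might infer that main effects will be reported as the treatment effect, but no passage says that. The fault is in what the rule offers once the gate is passed.

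**Follow-up tests are planned, and exact contrasts are often left to an analysis plan.** This also stands in part. The Tukey post hoc tests mean that the plan does not turn to averages alone, and an unseen plan may name the contrasts. Even so, the tests are only to be considered and no comparison is given. The reversed rule is stated outright, not left to another document.

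**Two stronger readings are not supported.**
- A reader might infer that no T1 contrast is isolated for any outcome. For steps and moderate-to-vigorous activity that is false, as Step 4 shows.
- A reader might infer that the 2-df test loses power when an effect fades by T2. A between-subjects F test at f = 0.25 and N = 156 gives power of 0.80 with 2 df against 0.87 with 1 df, but it does not model the planned repeated-measures interaction. In the simulated fading scenario the 2-df interaction was significant in 84% of runs and the T1-T0 change contrast in 81%. No power argument is made here.

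**Conclusion.** Wrong as written. The rule reverses normal practice and, for every primary outcome to which the model is applied, points to quantities that do not estimate the treatment effect. For a true T1 difference of 0.50 SD the group main effect is 0.25 SD with two occasions and 0.17 to 0.33 SD with three.

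These averages follow from the design and need only a zero expected difference at T0 and the stated T2 scenarios. They do not depend on sample size, correlation or clustering. The simulated percentages do depend on the assumptions in Step 3 and serve only as illustration.

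The separate point about mixing T1 with T2 is limited to the three-occasion self-reported outcomes. There the stated analysis does not test the effect and its maintenance as the two questions that the Overview poses. Main effects remain defined as averages, so the accurate criticism is that they do not estimate the treatment effect, not that they have no meaning. Using a repeated-measures interaction is an accepted choice and is not itself a fault.

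**What to change.** In Data Analysis:

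1. Delete the main-effects sentence, or replace it with: *if the interaction is significant, simple effects (group differences at each occasion) will be interpreted, not main effects.*
2. Name the group-by-time interaction as the test of the intervention effect. For accelerometer outcomes nothing further is needed, since this is the T1-T0 between-group contrast.
3. For self-reported activity and healthy eating, report the between-group contrast at T1 relative to T0, with a 95% CI, as the intervention effect. Report the contrast at T2 relative to T0 separately, as the answer on maintenance.

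The cost is analysis wording only, with no change to data collection or sample size. The article reports SF2.0 data acquisition as ongoing, so for that trial the change can be made and dated before analysis.

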## Results

This study is funded by the German Federal Ministry of Education and Research and ethically approved by the Karlsruhe Institute of Technology. For both trials, it is hypothesized that the apps will positively influence physical activity and healthy eating in the whole family. Furthermore, SF2.0 is expected to produce stronger effects (ie, higher effect sizes) as compared to SF. SF app development and piloting are completed. Data acquisition for the SF trial is terminated and discontinued due to the COVID-19 pandemic. SF2.0 app development and piloting are completed, and data acquisition is ongoing. The recruitment of the participants for the SF2.0 trial started in February 2020. The results for SF are expected to be published in mid-2021, and the results of SF2.0 are expected for mid-2022.

## Discussion

### Overview

The aim of the SF project is the development, implementation, evaluation, and refinement of an mHealth intervention to increase physical activity and healthy eating at individual and family level. Extending the previous research, the behavior of children *and* parents is targeted in order to induce individual behavior changes that are anchored in daily family life. Moreover, several behavior change techniques were included, which contribute to the fulfillment of the basic psychological needs according to the self-determination theory [46,47]. We examined whether (1) mHealth interventions (SF, SF2.0) elicit meaningful increases in physical activity levels and healthy eating in children as well as adults as compared to controls (no mHealth intervention), (2) changes are maintained after the intervention period, and (3) intervention effects can be strengthened by the addition of app-based features and JITAIs (SF2.0).

### Innovative App Features: Strengths, Challenges, and Limitations

The SF and SF2.0 target the family as a whole. SF and SF2.0 aim to promote parents’ as well as children’s behavior by focusing on family level behavioral goals that could only be achieved if all family members collaborate. Although most apps that aim to improve physical activity and healthy eating focus on an individual’s behavior and comprise social features by the facilitation of social comparisons [79], both SF apps focus on collaborative group behavior and collective goal setting within a family-based setting. Furthermore, as known from sports psychological team theories, individual team members have the capacity to influence the behavior of other team members, thereby resulting in a state of team synergy, which can be loosely described as performance capacity that is more than the sum of its parts [80,81]. One advantage of using a group intervention is that studies have shown groups to work more effectively for a given goal (ie, aiming for a healthier lifestyle or increasing physical activity [82]). In one of the first studies in the field of social psychology, Triplett [83] found that people perform tasks better when the social context includes other people than when individuals complete a task alone. Subsequent findings validated Triplett’s results, and other experiments have shown that the presence of others can increase performance in many types of tasks, including jogging, playing pool, lifting weights, and working on mathematics and computer problems [84-86]. The tendency to perform tasks better or faster in the presence of others is known as social facilitation. This study aims to take the advantage of the social facilitation theory by involving the whole family as a social system into the intervention.

A constraining factor might be that family sizes and ages within families may vary. As studies have shown that there is an inverse relationship between family size, parental resources, and children’s educational performance [87], family size might also affect intervention success. However, there is currently a lack of knowledge about this relationship regarding behavior change or accomplishment of healthy lifestyles in families. Depending on family size distribution, families of different sizes will be compared if possible. However, future studies need to focus on and examine whether bigger families have advantages or disadvantages regarding intervention effects compared to smaller families. A further constriction might be the age range, especially of children and adolescents. Since this study includes the whole family, children of different ages and with different needs and perceptions are addressed in a similar way by the app, which might affect the intervention effects. Finally, SF and SF2.0 are based on sophisticated technical issues. EMA is used to assess physical activity (accelerometers), healthy eating (diaries), and psychosocial correlates. The inclusion of device-based and self-reported measures of physical activity provides a more comprehensive picture of the actual amount of physical activity. However, the synchronization of accelerometer-based data among multiple users also enhances the complexity of the app and is a potential source of problems caused by the Bluetooth low energy interface.

To the best of our knowledge, this is the first study implementing a mobile app to promote individual physical activity and healthy eating of children/adolescents and their parents in a family-based setting. Evidence-based strategies are integrated within a collaborative approach, which is characterized by setting family goals and collaborative striving for the achievement of these goals. This principle is contrary to several commercial apps or social media–based interventions, fostering a competitive environment through social comparisons among users. Further, the app in this study does not require external goal-setting but rather encourages the whole family to set their own goals and to plan joint activities and meals, which fosters communication within the family. Moreover, the additional inclusion of app features such as the interactive goal-setting coach, gamification, JITAIs, and EMAs in SF2.0 may exploit the potential of an mHealth intervention by means of its interactive and time-adapted nature [58,88]. Thus, JITAIs target to promote physical activity and healthy eating during those time periods when the individual is at high risk for physical inactivity and unhealthy eating patterns. Furthermore, user engagement will be monitored with these sophisticated tools, thus enabling the identification of the potential effects of regular app usage on the change of health habits.

### Potential Methodological Issues

Based on literature regarding theories on behavior change (ie, the transtheoretical model [89,90]), an intervention duration of 3 weeks might not be sufficient [35]. This might also be true for the follow-up at 4 weeks following the intervention, which might not be an appropriate time point to measure the maintenance of behavior change. However, mHealth intervention studies have revealed significant behavior change effects even with intervention durations of only 1 [91], 2 [92], and 3 weeks [93]. In a similar vein, a recent meta-analyses on mobile apps for diet management showed that interventions with longer duration were not generally more effective [35]. To our knowledge, there is currently no common accepted standard and sufficient empirical evidence for devising an “ideal” intervention duration, although a dose-response relationship appears very plausible. Moreover, as we examine families in their natural setting, there are also practical constraints. In Germany, a continuous school period lasts for a maximum of 6 to 8 weeks, followed by a vacation period. In order to conduct the core assessments, including pretesting and posttesting accelerometry, during 1 continuous school period, we needed to condense the actual interventions per family to 3 weeks. Longer intervention periods would inevitably mean that there is a confounding between assessment periods (school time vs vacation). Another issue is that participants have to use an additional smartphone to run the SF and SF2.0 app while also wearing the accelerometer on the hip. This burden might limit user engagement, which, however, can be controlled for by analysis of app usage data.

### Conclusion

Taken together, SF and SF2.0 expand on the existing body of evidence as they investigate the influence of a theory-based mHealth intervention targeting physical activity and healthy eating in a collective family-based setting. The major advantage of this smartphone app is that it facilitates behavior change at the individual level and the family level as the implemented strategies address changes in daily family life. Furthermore, motivation-enhancing features based on gamification strategies (ie, personal coach in SF2.0) and a JITAI approach matching interventions to individual needs is expected to induce positive behavioral changes at the individual and family level. Project information, updates, and results can be found on the project homepage [57].

## Appendix

Multimedia Appendix 1 CONSORT-eHEALTH checklist (V 1.6.1)

## Abbreviations

EMA: ecological momentary assessment
JITAI: just-in-time adaptive intervention
mHealth: mobile health
SF: SMARTFAMILY
